## Abstract

**Background:**

Chronic non-specific low-back pain (LBP) is one of the most common and expensive musculoskeletal disorders in industrialized countries. Similar to other countries in the world, LBP is a common health and socioeconomic problem in Iran. One of the most widely used modalities in the field of physiotherapy for treating LBP is therapeutic ultrasound. Despite its common use, there is still inconclusive evidence to support its effectiveness in this group of patients. This randomised trial will evaluate the effectiveness of continuous ultrasound in addition to exercise therapy in patients with chronic LBP.

**Methods and design:**

A total of 46 patients, between the ages 18 and 65 years old who have had LBP for more than three months will be recruited from university hospitals. Participants will be randomized to receive continuous ultrasound plus exercise therapy or placebo ultrasound plus exercise therapy. These groups will be treated for 10 sessions during a period of 4 weeks. Primary outcome measures will be functional disability and pain intensity. Lumbar flexion and extension range of motion, as well as changes in electromyography muscle fatigue indices, will be measured as secondary outcomes. All outcome measures will be measured at baseline, after completion of the treatment sessions, and after one month.

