### Sample size

According to the data of a randomised pilot study which involved 10 patients, the effect size based on the Functional Rating Scale (FRI) was calculated to be 1.83. Since the number of patients in the pilot study was few, we calculated the sample size for the current study using an effect size of 0.8. Considering the results of our previous article [18] and the results obtained from the pilot study we expect ultrasound to be more effective and have chosen a one-sided test to calculate the sample size. Assuming alpha and power to be 0.05 and 0.8, in a one-tailed test the total sample size needed is 42 (21 patients in each group). Accounting for 10% drop-out, the total number of patients required is 46 (23 patients in each group).

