### Outcome measures

Patient's specifications such as age, sex, body mass index, and pain history will be recorded in a demographic questionnaire at the baseline assessment. All primary and secondary outcome measures will be measured by the researcher at baseline, the final treatment session (after 4 weeks), and at a follow-up measurement after 3 months.

Primary outcome measures will be

• Functional disability due to LBP measured by the Functional Rating Index.

• Pain measured on a visual analogue scale (VAS)

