### Data collection and analysis

An intention-to-treat analysis will be performed. In the case of dropouts and withdrawals, the last recorded values for the main outcome measures will be used in the analysis. We will check if the two groups are similar for the most important demographic characteristics and all outcome measures at baseline. In case of finding any differences we will adjust for them in a regression analysis. Between-group differences in the change of scores of all outcome measures will be analysed using the Statistical Package for the Social Sciences (SPSS) version 17. We will consider whether the data meet parametric or non-parametric conditions. If parametric, ANOVA, independent and paired t-tests will be used and in case of non-parametric conditions we will use Kruskal-Wallis, Mann-Whitney and Wilcoxon signed-rank tests. All analyses will be performed blinded for treatment allocation.

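### Two unranked primary outcomes at two visits, with no primary visit or success rule, do not fit a sample size set for one FRI-based test

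*Protocol article*

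**What the plan says.** The abstract (Methods and design) gives two primary outcomes without ranking them: "Primary outcome measures will be functional disability and pain intensity". The Outcome measures section repeats both as primary, disability on the FRI and pain on a visual analogue scale (VAS).

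Both are assessed twice after baseline. The Outcome measures section has them measured "at baseline, the final treatment session (after 4 weeks), and at a follow-up measurement after 3 months". The abstract times the second visit differently: "All outcome measures will be measured at baseline, after completion of the treatment sessions, and after one month". Neither place names a primary visit.

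The Sample size section starts from a 10-patient pilot in which "the effect size based on the Functional Rating Scale (FRI) was calculated to be 1.83". It reduces this to 0.8 and sizes one one-tailed test at alpha 0.05 and power 0.8: 42 evaluable patients, or 46 with drop-out. Pain is not mentioned there.

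The Data collection and analysis section says: "Between-group differences in the change of scores of all outcome measures will be analysed". It lists ANOVA, t-tests and non-parametric counterparts. It gives no test level, sidedness, order of testing or rule for combining the two primary outcomes.

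**The concern.** Alpha 0.05 and power 0.8 describe one test. With two outcomes of equal rank, what they mean depends on a success rule that the protocol does not give. If either outcome is enough, the trial has more than one chance of a false claim and 0.05 is not held. If both are needed, 0.05 is held, but the chance of success is below the power for one outcome alone.

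Two visits with no primary one widen the choice further. The Sample size section says the investigators expect ultrasound to be more effective, and the aim is to inform practice on a disputed treatment. Without a rule fixed in advance, effectiveness could be claimed from whichever outcome and visit turned out favourable, and that choice cannot be repaired credibly once the data are seen.

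**Working it through.** **Inputs.** From the Sample size section: standardised effect 0.8, one-tailed alpha 0.05, power 0.8, 21 per arm, 10% drop-out. From the abstract and Outcome measures: two primary outcomes and two post-baseline visits. Assumed, because the protocol does not give them: 5% for each test, the correlations between outcomes and between visits, and an effect of 0.8 on VAS.

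**1. The plan's own figure.** For a two-sample t-test with 21 per arm, the noncentrality is 0.8 × √(21/2) = 2.59 on 40 degrees of freedom. One-sided power at 0.05 is 81.7%; with 20 per arm it is 79.9%. So 21 per arm (42 in all) reproduces. For drop-out, 42 × 1.1 = 46.2 and 42/0.9 = 46.7, so the stated 46 is reproduced to within one patient. The sample size is sound for one test.

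**2. Any one result suffices.** For k independent tests at 5%, the error is 1 − 0.95^k:

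- k = 2: 1 − 0.95² = 9.75%
- k = 4: 1 − 0.95⁴ = 18.5%

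Independence is the upper end. The FRI itself covers pain as well as function, and the same patients are seen at both visits. The table simulates correlated normal statistics (2,000,000 draws) with no true effect; entries are one-sided / two-sided.

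| Correlation between outcomes | Two tests, one visit | Four tests, visit correlation 0.5 | Four tests, 0.7 | Four tests, 0.9 |
|---|---|---|---|---|
| 0 | 9.8% / 9.8% | 16.8% / 17.3% | 15.5% / 16.0% | 13.1% / 13.6% |
| 0.5 | 8.8% / 9.1% | 15.0% / 16.2% | 13.8% / 14.8% | 11.8% / 12.6% |
| 0.7 | 8.0% / 8.4% | 13.8% / 14.9% | 12.6% / 13.7% | 10.8% / 11.6% |
| 0.9 | 6.8% / 7.0% | 11.8% / 12.6% | 10.8% / 11.5% | 9.2% / 9.8% |

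The range is about 7-10% for two tests. For four tests it is about 9-17% under these correlations, and 18.5% if all four are independent.

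**3. Both outcomes required at one named visit.** The error rate is at most 5%, because neither outcome alone can produce a claim. Power at 21 per arm, one-sided 0.05, effect 0.8 on each outcome:

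- correlation 0: 0.817² = 66.7%
- for correlation ρ > 0: 1 − 2Φ(c − m) + Φ₂(c − m, c − m; ρ), with m = 2.59 and c the 95% point of t on 40 degrees of freedom. This gives 69.3% at 0.3, 71.2% at 0.5 and 73.6% at 0.7.

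Joint power can never exceed the 81.7% for FRI alone. It reaches 80% only if pain succeeds almost every time disability does.

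**4. Both kept as alternatives, with alpha split.** At one-sided 0.025 each, power per outcome at 21 per arm is 71.6%. Restoring 80% takes 26 per arm: 52 evaluable, and 52/0.9 = 57.8, so 58 recruited.

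**The case against.** A reader might infer that the trial's false-positive rate is known to be well above 5% because four primary tests are each run at 5%. The protocol does not support that, for three reasons.

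- The 0.05 appears only in the Sample size section; the analysis section states no test level.
- Four separate tests is one reading. One ANOVA per outcome across both visits also fits the text and would give two primary tests, for which the inflation is smaller.
- Inflation requires a rule that any single success is enough, and the protocol nowhere says so. If both outcomes are required, the error rate is held and the cost is power.

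It can also be said that testing order and multiplicity rules are commonly left to an analysis plan, which is not shown, and that this article is condensed. That is fair, and the absence of such a rule is not by itself the point. What stands is what the article fixes: two unranked primary outcomes beside one alpha and one power figure for a single test. An analysis plan could settle this by ranking the outcomes, which is the remedy proposed below.

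Finally, the design effect of 0.8 is a rounded-down standardised value and could be applied to pain as well. Doing so does not rescue the power: step 3 does exactly that and still finds 67-74%.

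**Conclusion.** The point holds as a mismatch within the protocol. For two unranked primary outcomes, the stated alpha fails if any one result suffices: about 7-10% for two tests and 9-18.5% for four, at an assumed 5% per test and over assumed correlations from 0.9 down to 0. The stated power fails if both must succeed at one visit: about 67-74% one-sided instead of 80%, assuming an effect of 0.8 on VAS and a correlation of 0 to 0.7. A much larger effect on pain would bring joint power closer to its ceiling of 81.7%, but the protocol gives no pain effect to support that.

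Since no rule is given, the error rate is undefined and uncontrolled; it is not shown to exceed 5%. The sample size calculation itself is correct for one FRI test. This should be fixed, and can be fixed without changing the design.

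**What to change.** Name one primary outcome at one visit before unblinding. FRI at end of treatment is the natural choice: the sample size was built on the FRI, and that visit is not affected by the conflict over follow-up timing. Test VAS at the same visit only if FRI is significant, then the follow-up comparisons in a stated order, each only if the one before succeeded. Use the stated alpha throughout and state the sidedness in the analysis section. This holds the overall level, costs FRI no power and keeps 46 patients. It needs a change of wording and a registry update.

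The downside is that pain can be claimed only after disability succeeds, although the Background gives the aim as both pain and function. If both outcomes must stay primary, use Holm at one named visit and restate the power: at 21 per arm it is at least 71.6% per outcome, the Bonferroni floor at one-sided 0.025.

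In either case, reconcile the follow-up time (one month in the abstract, three months under Outcome measures) before any follow-up test is placed in the order.

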**Discussion:**

The results of this trial will help to provide some evidence regarding the use of continuous ultrasound in chronic LBP patients. This should lead to a more evidence-based approach to clinical decision making regarding the use of ultrasound for LBP.

**Trial registration:**

Netherlands Trial Register (NTR): NTR2251

## Background

Low back pain (LBP) is the most frequent self-reported type of musculoskeletal pain, is often recurrent, and has important socio-economic consequences. Estimates of the prevalence of LBP and are as high as 33% for point prevalence, 65% for 1-year prevalence, and 84% for lifetime prevalence [1].

Similar to other countries in the world, LBP is a common health and socioeconomic problem in Iran. In a cross-sectional study in one of the largest car-manufacturing companies in Iran, the 1-year prevalence of self-reported LBP was 21% (20% males and 27% females). The prevalence rate of absence due to LBP was 5% per annum [2]. As part of a World Health Organization study, LBP was detected in 15.4% of the population under survey in Tehran (urban area) [3] and in 23.4% of the population in rural areas in Iran [4].

LBP is defined as pain and discomfort in the lumbosacral region, below the twelfth rib and above the gluteal crease. According to the recommended diagnostic triage, three types of back pain can be defined: 1) non-specific low back pain; 2) back pain with nerve root symptoms; and 3) back pain resulting from serious pathology (e.g. malignancy, fracture, ankylosing spondylitis, infection). Non-specific LBP, in which there is no recognized patho-anatomic cause, is usually a benign condition but without appropriate management can develop into chronic LBP. Using the traditional classification system, LBP is also categorized according to its duration from onset, as acute (<6 weeks), sub-acute (6 weeks - 12 weeks), and chronic (>12 weeks) [5,6]. Chronic LBP remains a common problem that many practitioners have to deal with in primary care, secondary care, and occupational health care.

The main objective of treatment for chronic LBP is for the patient to return to their desired level of activities and participation, as well as the prevention of chronic complaints and recurrences [7]. Many treatments are commonly used for LBP such as medication, physiotherapy, and surgery. Many of these interventions have been evaluated in randomized controlled trials and systematic reviews. Evidence shows that the effectiveness of some of the interventions is supported (e.g. exercise), while it shows that other interventions are not effective for LBP (e.g. laser therapy and traction) [8-10]. The number of randomized trials varies widely across interventions, from 61 for exercise therapy to 19 on back school and 4 on transcutaneous electrical nerve stimulation (TENS) [9,11,12].

Therapeutic ultrasound is used frequently in the treatment of LBP by many physiotherapists around the world and after more than 60 years of clinical use, there is still great controversy over its usefulness [13-16]. According to two recent clinical guidelines, the UK NICE guideline http://guidance.nice.org.uk/CG88 and the COST B13 European guideline for the management of LBP [5], there is no evidence regarding the benefit of using electrotherapy modalities such as interferential, laser, TENS, and ultrasound even though these modalities are commonly used in physiotherapy practice. The guidelines and recent systematic reviews [17] of therapeutic ultrasound have highlighted a need for further research to investigate the true effect of these modalities in the context of well conducted randomized controlled trials. As the application of ultrasound may have adverse effects for patients with LBP (e.g. because of the transmission of thermal energy), it is important to know whether the benefits outweigh the risks of this commonly used intervention.

This study will aim to investigate the effects of continuous ultrasound with pre-defined doses, in comparison with sham ultrasound, delivered in combination with a semi-supervised exercise program on pain intensity and function in patients with chronic LBP. This study has received ethical approval from the Tehran University of Medical Sciences.

## Methods

### Study design

A single blind randomized controlled trial in which participants with chronic LBP will be randomized to one of two treatment groups:

• Continuous ultrasound + semi-supervised exercise therapy

• Sham ultrasound + semi-supervised exercise therapy

### Study population

Patients aged between 18 and 65 years who present with chronic LBP will be recruited for this study.

### Inclusion and exclusion criteria

Patients with LBP who have pain for more than 3 months will be eligible. Patients with nerve root symptoms, underlying systematic or visceral disease, and specific conditions such as neoplasm, fractures, spondylolysthesis, spondylolysis, spinal stenosis, ankylosing spondylitis, previous low back surgery, and pregnancy will be excluded. The researcher will also ask potential participants if they take any medication for specific psychological problems in which case they will be excluded.

### Recruitment procedures

Recruitment will take place in two steps: firstly, orthopaedic surgeons from three university hospitals in Tehran, Iran will identify potentially eligible patients and refer them to the research centre at the Rehabilitation Faculty of Tehran University of Medical Sciences. Secondly, the researcher will conduct another screening for inclusion and exclusion criteria and make the final decision regarding eligibility. If eligible, the patient will be provided with oral and written information about the study. After having signed a consent form, patients will be randomized to one of the two treatment groups.

### Randomization

Opaque, sealed envelopes will be prepared to the total number of patients using a computer generated randomization schedule, with half of the envelopes being allocated to each group ensuring equal number of subjects in each group.

The list and the envelopes will be prepared by a statistician who is not involved with the study prior to commencement of the trial to ensure concealment of patient allocation.

### Sample size

According to the data of a randomised pilot study which involved 10 patients, the effect size based on the Functional Rating Scale (FRI) was calculated to be 1.83. Since the number of patients in the pilot study was few, we calculated the sample size for the current study using an effect size of 0.8. Considering the results of our previous article [18] and the results obtained from the pilot study we expect ultrasound to be more effective and have chosen a one-sided test to calculate the sample size. Assuming alpha and power to be 0.05 and 0.8, in a one-tailed test the total sample size needed is 42 (21 patients in each group). Accounting for 10% drop-out, the total number of patients required is 46 (23 patients in each group).

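### The 80% power rests on a one-sided 5% test that the analysis section does not carry over; a two-sided 5% test gives about 72% to 76%

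*Protocol article*

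**What the plan says.** Protocol article, Sample size: a pilot in 10 patients gave an effect size of 1.83 on the Functional Rating Index. Because the pilot was small, the authors reduced it: "we calculated the sample size for the current study using an effect size of 0.8". On direction, citing their earlier article and the pilot, they write: "we expect ultrasound to be more effective and have chosen a one-sided test to calculate the sample size". The inputs and result follow: "Assuming alpha and power to be 0.05 and 0.8", and "in a one-tailed test the total sample size needed is 42 (21 patients in each group"). A 10% drop-out allowance brings the total to 46, or 23 per arm.

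Protocol article, Data collection and analysis: the analysis is by intention to treat, with last recorded values carried forward for drop-outs, and compares changes in score between groups. On tests: "If parametric, ANOVA, independent and paired t-tests will be used and in case of non-parametric conditions we will use Kruskal-Wallis", followed by the Mann-Whitney and Wilcoxon signed-rank tests. The section gives neither a direction nor a significance level. Regression adjustment is planned only if the groups are found to differ at baseline.

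Protocol article, Background: ultrasound may have adverse effects in these patients, and "it is important to know whether the benefits outweigh the risks of this commonly used intervention". The same section reports continuing controversy over whether ultrasound is useful. The Discussion says that earlier trials could not settle the matter.

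**The concern.** Power belongs to a particular test at a particular level. Here the sample size is tied to a one-sided 5% test, but the text makes that choice only for the calculation: "have chosen a one-sided test to calculate the sample size". Nothing in the analysis section repeats it, and the ANOVA F test and Kruskal-Wallis test cannot be directional. Two readings are therefore open, and each has a cost.

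- **Two-sided 5% analysis.** The trial does not have its stated 80% power at d = 0.8.
- **One-sided 5% analysis.** The power stands. But ultrasound is declared superior at a threshold equal to two-sided p < 0.10, and a difference in favour of sham could not be declared significant. The support for this is an expectation drawn from a 10-patient pilot, which the authors themselves discount when choosing the effect size, and from their own earlier article. Expecting benefit does not rule out the opposite result, and the Background presents the question as unsettled.

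While the choice is open, a result with two-sided p between 0.05 and 0.10 in favour of ultrasound could be called significant or not after the data are seen.

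**Working it through.** **Inputs, all from Sample size:** d = 0.8 (SD = 1), alpha 0.05, target power 0.80, 21 per arm evaluable, 23 per arm randomised, equal arms.

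**Method.** Two-sample t-test with n per arm: df = 2n − 2 and noncentrality δ = d·√(n/2). One-sided power is P(T > t[0.95, df]). Two-sided power is P(|T| > t[0.975, df]). T is noncentral t with parameter δ.

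**Step 1. The plan's own figure (one-sided 5%).**
- n = 20: δ = 0.8·√10 = 2.530, critical value 1.686, power 79.9%.
- n = 21: δ = 0.8·√10.5 = 2.592, critical value 1.684, power 81.7%.

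The smallest n reaching 80% is 21 per arm, 42 in total. The stated number is reproduced.

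**Step 2. Same design, two-sided 5%.**

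| n per arm | Total | δ | Critical value | Power |
|---|---|---|---|---|
| 21 | 42 | 2.592 | 2.021 | 71.6% |
| 23 | 46 | 2.713 | 2.015 | 75.6% |
| 25 | 50 | 2.828 | 2.011 | 79.1% |
| 26 | 52 | 2.884 | 2.009 | 80.7% |

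The row for 46 matches the planned intention-to-treat analysis if the carried-forward values leave the effect at 0.8. If they dilute it, power is lower. Reaching 80% two-sided needs 26 per arm.

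**Step 3. Effect detectable with 80% two-sided power.** Solving for d gives 0.89 at 21 per arm and 0.84 at 23 per arm.

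**Step 4. How far baseline adjustment could help.** The documents give neither the baseline to follow-up correlation r nor the SD to which d refers, so both are assumptions here. With equal SDs at both times, adjustment for baseline (ANCOVA) leaves a residual SD of σ·√(1 − r²). The effective d is then:
- 0.8/√(1 − r²) if d is on the follow-up SD;
- 0.8·√(2/(1 + r)) if d is on the change-score SD, which is σ·√(2(1 − r)).

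Two-sided 5% power at 21 per arm, df = 39:

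| r | d on follow-up SD: effective d | Power | d on change SD: effective d | Power |
|---|---|---|---|---|
| 0.3 | 0.839 | 75.5% | 0.992 | 88.0% |
| 0.5 | 0.924 | 83.1% | 0.924 | 83.1% |
| 0.7 | 1.120 | 94.3% | 0.868 | 78.3% |

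Every entry exceeds the unadjusted 71.6%, but the range is wide and two of the six entries stay below 80%.

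**The case against.** The one-sided test is declared openly, 42 is correct for it, and the analysis section is silent rather than in conflict. A journal article commonly leaves the direction of each test to the full protocol or analysis plan, so silence alone is no finding. The listed tests are a general menu: the two-group members, the independent t-test and Mann-Whitney, can be run one-sided. The authors were also cautious in cutting the pilot effect from 1.83 to 0.8.

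Much of this stands. A reader might infer three stronger points that the documents do not support:
- **That the sample size is miscalculated.** It is not; Step 1 reproduces it.
- **That the article commits to a two-sided analysis and so contradicts itself.** It does not. The 72% to 76% is conditional on a two-sided test.
- **That a one-sided test stops the trial from reporting harm.** It does not. Adverse effects, and a mean difference favouring sham, could still be reported; only a claim of significance in that direction is lost. Likewise, a one-sided 5% test keeps its declared 5% error rate. It is lenient relative to the common 2.5% per side, a convention that the article does not adopt.

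What the objection does not remove is that the article itself makes a positive choice, gives a weak reason for it, ties it to the sample size only, and lists tests that cannot all deliver it.

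**Conclusion.** The concern holds in this limited form. The 80% power is valid only for a one-sided 5% test, whose sole stated justification is that benefit is expected and which the analysis section does not take up. Under a two-sided 5% t-test at d = 0.8, power is about 72% with 42 patients and about 76% with all 46, a shortfall of roughly 4 to 8 percentage points. The upper figure assumes that carrying last values forward does not dilute the effect. Under a one-sided 5% test the power claim stands, and the cost is instead the lenient threshold and the inability to declare a difference favouring sham significant.

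This should be fixed. It does not invalidate the design: the shortfall is moderate, it arises under only one of the two readings, and wording resolves it.

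**What to change.** In Sample size and in Data collection and analysis, state that all between-group tests are two-sided at 5% and reported with 95% confidence intervals. Keep 46 patients. Restate the power as about 72% with 42 evaluable patients and about 76% with 46 at d = 0.8, or equivalently a detectable effect of 0.89 or 0.84 at 80% power.

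Prespecifying baseline-adjusted ANCOVA, instead of adjusting only when a baseline difference is found, may recover some of the power. It should be offered with its assumptions: the gain depends on r and on the SD behind d, as Step 4 shows, so no single recovered figure should be quoted unless both are stated.

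Cost: wording only and no added patients. The downside is that the stated power becomes less favourable.
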